# Combination of multi-modal MRI radiomics and liquid biopsy technique for preoperatively non-invasive diagnosis of glioma based on deep learning: protocol for a double-center, ambispective, diagnostical observational study

**DOI:** 10.3389/fnmol.2023.1183032

**Published:** 2023-05-02

**Keywords:** glioma, radiomic, liquid biopsy, circulating tumor cell, histopathology, molecular pathology, diagnosis

## Abstract

**Background:**

2021 World Health Organization (WHO) Central Nervous System (CNS) tumor classification increasingly emphasizes the important role of molecular markers in glioma diagnoses. Preoperatively non-invasive “integrated diagnosis” will bring great benefits to the treatment and prognosis of these patients with special tumor locations that cannot receive craniotomy or needle biopsy. Magnetic resonance imaging (MRI) radiomics and liquid biopsy (LB) have great potential for non-invasive diagnosis of molecular markers and grading since they are both easy to perform. This study aims to build a novel multi-task deep learning (DL) radiomic model to achieve preoperative non-invasive “integrated diagnosis” of glioma based on the 2021 WHO-CNS classification and explore whether the DL model with LB parameters can improve the performance of glioma diagnosis.

**Methods:**

This is a double-center, ambispective, diagnostical observational study. One public database named the 2019 Brain Tumor Segmentation challenge dataset (BraTS) and two original datasets, including the Second Affiliated Hospital of Nanchang University, and Renmin Hospital of Wuhan University, will be used to develop the multi-task DL radiomic model. As one of the LB techniques, circulating tumor cell (CTC) parameters will be additionally applied in the DL radiomic model for assisting the “integrated diagnosis” of glioma. The segmentation model will be evaluated with the Dice index, and the performance of the DL model for WHO grading and all molecular subtype will be evaluated with the indicators of accuracy, precision, and recall.

**Discussion:**

Simply relying on radiomics features to find the correlation with the molecular subtypes of gliomas can no longer meet the need for “precisely integrated prediction.” CTC features are a promising biomarker that may provide new directions in the exploration of “precision integrated prediction” based on the radiomics, and this is the first original study that combination of radiomics and LB technology for glioma diagnosis. We firmly believe that this innovative work will surely lay a good foundation for the “precisely integrated prediction” of glioma and point out further directions for future research.

**Clinical trail registration:**

This study was registered on ClinicalTrails.gov on 09/10/2022 with Identifier NCT05536024.

## Background

Gliomas are the most common primary intracranial malignancies, accounting for 27% of all primary brain tumors, and ~100,000 people are diagnosed with diffuse gliomas worldwide each year (Ostrom et al., 2014). To date, “integrated diagnosis” was considered the gold standard for glioma diagnosis, which combines histopathology, molecular pathology, and World Health Organization (WHO) grade (Balana et al., 2022). Previous glioma diagnostic criteria have primarily relied on histopathological biopsies, while histological classification has traditionally been determined based on tumor morphology, resulting in intra-observer variability due to intra-tumor spatial heterogeneity and sampling errors (van den Bent, 2010; Jin et al., 2021; Wijethilake et al., 2021). In addition, Traditional histopathology is somewhat difficult to explain why patients with the same pathology have significantly different survival. Over the past decade, advances in molecular pathology and histopathology detection techniques have deepened our understanding of the molecular features and biology of gliomas (Ferris et al., 2017; Acs et al., 2020). Increasing evidence revealed the important role of molecular status in the “integrated diagnosis” of glioma (Weller et al., 2021; Gritsch et al., 2022; Horbinski et al., 2022). In particular, after the concept of molecular diagnosis was proposed by the 2016 WHO Central Nervous System (CNS) classification, the 2021 CNS classification (CNS5) reemphasized the importance of molecular biomarkers in gliomas diagnosis and treatment guidelines (Figure 1), including isocitrate dehydrogenase gene (IDH) mutation status, alpha-thalassemia/mental retardation syndrome X-linked (ATRX) deletion status, 1p19q deletion status, etc. (Louis et al., 2021; Weller et al., 2021). The objective is to classify the tumor subtypes more systematically and categorize the glioma patients with similar efficacy and prognosis into a subgroup.

**Figure 1 fig1:**
[figure not shown]
The distinction between 2016 and 2021 World Health Organization (WHO) Central Nervous System (CNS) tumor classification.

The current standard of therapy for gliomas is surgical resection followed by radiotherapy and/or chemotherapy based on clinical and tumor grade and molecular characteristics (Rudà et al., 2018; Weller et al., 2021). Preoperatively non-invasive and accurate early “integrated diagnosis” will bring great benefits to the treatment and prognosis of patients, especially for those with special tumor locations that cannot receive craniotomy or needle biopsy. Such special patients can take experimental therapy based on non-invasively diagnostic results. Although diagnostic criteria for molecular information are often based on tissue biopsy, other techniques, such as radiomics, radiogenomics, and liquid biopsy, have shown promise (Seow et al., 2018; Le Rhun et al., 2020; Müller Bark et al., 2020; Sareen et al., 2020; Jain and Chi, 2021; Sanvito et al., 2021; Balana et al., 2022). At present, conventional magnetic resonance imaging (MRI) scans are still the main method to assist in the diagnosis of gliomas, including pre-and post-contrast T1w, T2w, and T2w-FLAIR. Multimodal radiomics based on deep learning (DL) can comprehensively reflect the growth and morphological characteristics of gliomas, to conduct “integrated prediction” of gliomas (Gore et al., 2021).

## Related study

In recent studies, van der Voort et al. (2022) collected 1,508 patients with glioma from 16 institutions, they utilized the preoperative MRI scans to develop the multi-task conventional neural network (CNN) model and achieved the area under the receiver operator characteristic curve of the WHO grade (II/III/IV) with 0.81, IDH mutation status with 0.9, and 1p19q co-deletion status with 0.85 in the test set. Although the proposed model by R van der Voort et al. demonstrated high performance in glioma prediction, the relatively small number of molecular labels may limit the application of the model according to CNS5. The best DL model developed by Matsui et al. achieved an overall accuracy of 65.9% in predicting IDH mutation and 1p/19q co-deletion in 217 low-grade glioma patients (Matsui et al., 2020). Also, the multi-task CNN model constructed by Decuyper et al. achieved an accuracy of 94, 86, and 87% in predicting grades, IDH mutations, and 1p/19q co-deletion states in the external validation dataset with 110 patients (Decuyper et al., 2021). The model constructed by Luo et al. achieved 83.9 and 80.4% in external tests for histological and molecular subtype diagnosis (Luo et al., 2021).

In addition, there are many studies aimed to construct a non-invasive diagnostic model to predict WHO grade or single molecular markers based on the 2016 CNS classification (van der Voort et al., 2019; Bangalore Yogananda et al., 2020; Wijethilake et al., 2020; Casale et al., 2021; Choi et al., 2021; Pei et al., 2021), which is far from the comprehensive diagnosis concept of glioma and cannot meet the actual needs of non-invasive diagnosis of glioma under the constantly updated treatment concept. Therefore, a multi-task DL radiomics model for preoperatively and non-invasively predicting glioma grading and more significant molecular markers is urgently needed according to the latest 2021 CNS classification.

Radiomics has shown some feasibility in predicting tumor molecular pathology, it is ridiculous to administer precision-targeted therapy solely based on this prediction. Therefore, we hope to provide more clinical evidence for the molecular pathological diagnosis of glioma patients by using the liquid biopsy (LB) technique as an important complement to radiomics. Circulating tumor cells (CTC) is an important LB technique for tumor diagnosis, with the advantages of being non-invasive and accurate. Our previous study showed that CTC was an effective diagnostic marker for gliomas (Qi et al., 2021). Despite that no correlation was observed between CTC level and tumor histopathology, we found CTC closely related to IDH mutation status. Through the single-cell sequencing technique exemplified by multiple annealing and looping-based amplification cycles (MALBAC), researchers can obtain molecular pathology from CTC rather than tissue. These findings strongly supported that CTC can be an important complement to radiomics in glioma diagnosis. However, it must be noted that there is no common criterion for the detection and sequencing of gliomas CTC.

Based on the several limitations of the current diagnostic models of glioma, the combined methods of radiomics and LB have great potential to non-invasively diagnose glioma grading and molecular markers since they are both easy to perform. Furthermore, to our knowledge, there is no study for preoperatively non-invasive diagnosis of glioma in the context of LB-assisted radiomics.

Therefore, this study has the following objectives. First, according to the guidelines of the 2021 WHO-CNS classification, we will develop a multi-task DL model for simultaneous diagnosis of glioma classification (WHO II/III/IV) and all molecular subtypes, including IDH mutation, ATRX deletion status, 1p19q co-deletion, etc. Second, based on the same ultimate purpose of LB and radiomics, we innovatively put forward the concept and idea of combining LB technology and radiomics to investigate the performance of glioma diagnosis, and we hypothesize that adding CTC into the multitask DL model would improve the integrated diagnostic performance of glioma. This work will provide some clinical validation for this concept, hoping to supply some new ideas for subsequent research and support clinical decision-making.

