### Participant criterion

In this study, glioma patients from the Second Affiliated Hospital of Nanchang University, Renmin Hospital of Wuhan University, and one public database named the 2019 Brain Tumor Segmentation challenge dataset (BraTS) will be enrolled.

The inclusion criteria are as follows: (1) primary glioma; (2) aged over 18 years; (3) receiving surgical resection or needle biopsy for the first time; (4) without any radiotherapy and/or chemotherapy before a preoperative MRI scan.

The exclusion criteria are as follows: (1) secondary glioma; (2) undergone surgical treatment at admission; (3) missing MRI scan.

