### Sample size

A sample of 400 achieves 90% power to detect a difference of 0.1000 between the area under the ROC curve (AUC) under the null hypothesis of 0.7000 and an AUC under the alternative hypothesis of 0.8000 using a two-sided z-test at a significance level of 0.05000. The data are discrete (rating scale) responses. The AUC is computed between false positive rates of 0.000 and 1.000. The ratio of the standard deviation of the responses in the negative group to the standard deviation of the responses in the positive group is 1.000.

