### Radiomic model development methods

The research of Choi et al. (2021) indicated that the location and shape characteristics of tumors have an important relationship with the IDH classification of gliomas. After adding six location numerical features, 13 shape numerical features, and one age numerical feature, the classification accuracy of IDH was improved by 1.6–5.3 percent compared with the traditional resnet classification model on the three different datasets (Choi et al., 2021). Inspired by that, we designed a model that fuses tumor localization features and shape features for classification. Compared with the radiomics method used in Choi’s et al. (2021) work to obtain tumor location and shape information, obtaining these features directly through the target detection network does not require additional manual operations, which is significantly more time-saving and convenient.

Our model consisted of a segmentation network, target detection network, and classification network. The outputs of the target detection network were first processed and then combined with the numerical information of the CTC to input the classification network to classify the images.

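### The hypothesis that CTC improves the model has no described or sized comparison: the powered test sets one AUC against 0.70, and the only final classifier described takes CTC as input

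*Protocol article*

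**What the plan says.** The abstract's Background sets the aim to "explore whether the DL model with LB parameters can improve the performance of glioma diagnosis". The objectives at the end of Related study make this a hypothesis: "we hypothesize that adding CTC into the multitask DL model would improve the integrated diagnostic performance of glioma". It is the second of two objectives. The first is to develop the multi-task model itself.

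The Sample size section gives 400 patients and 90% power for a test framed as follows: "under the null hypothesis of 0.7000 and an AUC under the alternative hypothesis of 0.8000". The test is two-sided with alpha 0.05. No second model appears there, no correlation between models is given, and 0.70 is not described as the performance without CTC.

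Under Radiomic model development methods, the detection outputs are "combined with the numerical information of the CTC to input the classification network". The Figure 2 legend and the Classification part describe the same single route, with detection features and CTC features entering one multi-layer perceptron (MLP). The Classification index section names accuracy, precision and recall.

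Participant criterion says that patients from two hospitals and "one public database named the 2019 Brain Tumor Segmentation challenge dataset (BraTS) will be enrolled". Study design and Collection of peripheral blood obtain CTC from preoperative blood, the latter after written consent.

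**The concern.** The hypothesis concerns a difference between two models in the same patients. The powered test concerns the level of one model. A model in which CTC contributes nothing can pass that test on imaging alone, so a pass carries no information about CTC.

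The threshold makes this a practical matter. Related study cites an imaging-only model with test-set AUCs of 0.81 for grade and "IDH mutation status with 0.9, and 1p19q co-deletion status with 0.85 in the test set". All three exceed the alternative of 0.80.

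There is also a mismatch between population and model input. Public-database cases are enrolled, but the described classifier needs a blood measurement that those cases would not have. At stake is whether the study can answer its own second objective.

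**Working it through.** **1. What the sample size tests.** Inputs from the Sample size section: null AUC 0.70, alternative 0.80, two-sided alpha 0.05, power 90%, rating-scale data. The positive-to-negative split is not given; the ratio of 1.000 stated there is of standard deviations. With the binormal rating-scale variance (Obuchowski),

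V(AUC) = 0.0099 · exp(−A²/2) · [(5A² + 8) + (A² + 8)/R], A = 1.414 · z(AUC), R = negatives/positives,

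n₊ = (1.960·√V(0.70) + 1.2816·√V(0.80))² / 0.10², N = n₊(1 + R).

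At R = 3: V(0.70) = 0.1023 and V(0.80) = 0.0888, so n₊ = (0.6268 + 0.3820)²/0.01 = 101.8. That gives 102 positives and 306 negatives, N = 408. At R = 2.9, N = 401; at R = 1, N = 284; at R = 0.25, N = 402. So 400 is a coherent one-sample AUC figure at about 26% (or about 80%) positives. It is not shown to be wrong. The calculation contains no second model.

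**2. Can a useless CTC input pass?** Suppose imaging alone gives AUC 0.80 and CTC adds nothing. The chance of rejecting 0.70 is Φ[(0.10 − 1.960·√(V(0.70)/n₊)) / √(V(0.80)/n₊)]. At 50% positives (n₊ = 200, R = 1) this is (0.10 − 1.960 × 0.02694)/0.02444 = 1.93, or 97%.

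| Positives | Rejects 0.70, true AUC 0.80 |
|---|---|
| 10% | 57% |
| 20% | 84% |
| 26% | 90% |
| 30% | 93% |
| 50% | 97% |
| 80% | 90% |

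At a true imaging AUC of 0.85, rejection is about 92% even at 10% positives.

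**3. Power of the comparison that the hypothesis needs.** The article gives no base AUC, gain, correlation r or positive share, so these are assumptions. The Hanley-McNeil variance is

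v = [A(1 − A) + (n₊ − 1)(Q₁ − A²) + (n₋ − 1)(Q₂ − A²)]/(n₊n₋), where A is now the AUC, Q₁ = A/(2 − A), Q₂ = 2A²/(1 + A),

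with SE² = v₁ + v₂ − 2r√(v₁v₂) and power = Φ(0.05/SE − 1.960) for 0.85 to 0.90.

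At N = 400 and 50% positives, v₁ = 0.000377 and v₂ = 0.000255. With r = 0.5, SE = 0.01795, and 0.05/0.01795 − 1.960 = 0.83, which gives 80%.

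| Positives | SE, r = 0.5 | Power | SE, r = 0.7 | Power |
|---|---|---|---|---|
| 50% | 0.0180 | 80% | 0.0141 | 94% |
| 20% | 0.0261 | 48% | 0.0204 | 69% |
| 10% | 0.0363 | 28% | 0.0284 | 42% |

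With the rating-scale variance, the 50% row becomes 68% and 88%. All rows assume that all 400 patients have CTC and are out-of-sample. If only 200 did, at 50% positives, SE grows by √2 to about 0.0254 and 0.0199, and power falls to about 50% and 71%.

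**4. BraTS.** Enrolment includes a public image database, while CTC requires blood drawn by the study from consenting patients. The absence of CTC in BraTS cases follows from these two statements. The article does not say it in words, and nothing contradicts it.

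**The case against.** The strongest reply is that this is a condensed article, and that a with/without analysis could sit in the full protocol or SAP. A reader might infer that the hypothesis will never be tested; the article does not support that. Its abstract speaks of CTC being applied in addition to the radiomic model. The detection network also yields 14 class features before CTC is joined, so an imaging-only comparator could be built. What can be said is that no such comparison is described or sized here. The point does not rest on that silence, because the hypothesis, powered test, classifier and indexes are all stated and do not match.

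The 0.70/0.80 test may be meant for the first objective, and as a single-model criterion it is coherent. That stands. It means only that the 90% power belongs to that objective.

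The cited imaging AUCs cover grade, IDH and 1p/19q. None is cited for the other primary markers, so the argument from cited values is limited to those three.

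A reader might also infer that BraTS cases will receive a filler CTC value that turns the input into a marker of data source. No passage puts BraTS cases into the CTC classifier, counts them in the 400 or proposes imputation. The section on learning curves trains the classification part after the backbone, detection and segmentation parts, so BraTS could be confined to the first stage. What remains is that its role is unstated.

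**Conclusion.** The concern holds in this form: the article hypothesizes an incremental benefit of CTC but describes and sizes no comparison that addresses it. A result above 0.70 would not be evidence for CTC. With an assumed imaging AUC of 0.80 and no CTC effect, the sized test passes with about 90% probability or more at roughly 26% to 80% positives, and less often outside that range.

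The 90% power does not carry over to the CTC comparison. For an assumed gain from 0.85 to 0.90, paired power is 80–94% at 50% positives, 48–69% at 20% and 28–42% at 10%, for assumed correlations of 0.5 to 0.7. It is lower with the rating-scale variance, or when only CTC-measured, held-out patients count. It would therefore be wrong to infer that 400 patients are enough for every marker; the Discussion itself concedes that some subtypes have few training samples. That BraTS cases lack CTC is a secure inference. Any harm from how they are handled is not established.

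**What to change.** 1. Fit the final classifier twice, with and without the CTC inputs, on the same patients with measured CTC and the same splits. Report the paired AUC difference with a 95% CI (DeLong, for example) in out-of-sample patients, for markers with enough positives. Name this difference as the estimate that addresses the CTC hypothesis.
2. State that BraTS cases, and any patient without measured CTC, are used only for the backbone, detection and segmentation stage, which is already trained separately.
3. State that the 90% power applies to the single-AUC test and not to the CTC comparison. Add AUC and its between-model difference to the classification indexes.

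The cost is one extra training run of a small final network and revised wording; no new data are needed. The downside is fewer patients in the final stage and wide intervals for rare markers.

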## Methods

### Study design

The study design is a double-center, ambispective, diagnostical observational study, which enrolls glioma patients aged over 18 years. All eligible glioma patients will be recruited. Preoperative peripheral venous blood and postoperative tumor tissue samples will be collected to detect CTC characteristics and the latest glioma diagnosis based on the 2021 WHO-CNS tumor classification.

### Participant criterion

In this study, glioma patients from the Second Affiliated Hospital of Nanchang University, Renmin Hospital of Wuhan University, and one public database named the 2019 Brain Tumor Segmentation challenge dataset (BraTS) will be enrolled.

The inclusion criteria are as follows: (1) primary glioma; (2) aged over 18 years; (3) receiving surgical resection or needle biopsy for the first time; (4) without any radiotherapy and/or chemotherapy before a preoperative MRI scan.

The exclusion criteria are as follows: (1) secondary glioma; (2) undergone surgical treatment at admission; (3) missing MRI scan.

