### Outcomes

#### Primary outcomes

The molecular type of 2021 WHO-CNS classification will be the primary outcome, including IDH (mutant/wild), ATRX (retain/lost), 1p/19q (codel/intact), CDKN2A/B (retain/lost), TERT/EGRF/+7/−10 (retain/lost), H3.3 G34 (mutant/wild), H3K27M mutant.

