### Model development preprocess

Each patient in the dataset had MR scans of four sequences: T1C, T1, T2, T2 flair, and tumor mask, along with classification labels.

The goal of this network is to segment three regions of glioma, including enhanced tumor area (ET), non-enhanced tumor area (NET), and edema area (ED); The tumor’s location, size, and classification information obtained from the target detection network were combined with the CTC numerical feature to differentiate the histological type and molecular type.

Four different experienced neurosurgeons, who also received guidance from a senior neuroradiologist (>10 years of clinical experience), applied Segmentation and Segment Editor modules to manually segment the original MRI dataset. All scans have been co-registered to the same anatomical reference using a rigid transform method on the 3D-slicer registration module. Skulls of the brain MRI were removed by 3D-slicer software that can eliminate the influence of skull areas with high-intensity signals. MR scans often display intensity non-uniformities due to variations in the magnetic field. Therefore, N4 bias field correction was used before the image input. We use data augmentation to increase the size of the dataset. To prevent over-fitting in training, data augmentation was used to expand the dataset.

The data augmentation methods used are as follows: (1) Adding random noise to the voxel, the noise worth ranged between −0.1 times and 0.1 times the standard deviation of the voxel. (2) Image size was changed to the original 0.9–0.1 times. (3) Random rotation and translation, with rotation ranging from −20 to +20°, and translation ranging from −30 to +30 and −15 to +15, respectively. (4) Random flip.

According to the 2021 WHO classification criteria, the molecular types of glioma were divided into 11 subcategories, and the histological type was divided into three grades. The grades, segmentations, and subcategories labels of each patient were one-hot encoded. In the preprocessing step, anchor boxes of the tumors were automatically generated according to the segmentation labels. The anchor box was the ground truth of the target detection task.

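### BraTS 2019 cases feed a model with 2021-classification targets, but the article gives no route by which they could have 2021 labels, so grade and molecular training may rest partly on unsupported labels

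*Protocol article*

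**What the plan says.** All references are to the protocol article.

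- **Sources.** Participant criterion lists the two hospitals and adds that "one public database named the 2019 Brain Tumor Segmentation challenge dataset (BraTS) will be enrolled". The abstract's Methods paragraph says the three datasets "will be used to develop the multi-task DL radiomic model". Neither place limits BraTS to part of the model.
- **Target.** The first objective, at the end of Related study, is stated for the 2021 guidelines: "we will develop a multi-task DL model for simultaneous diagnosis of glioma classification (WHO II/III/IV) and all molecular subtypes". Under Primary outcomes, "The molecular type of 2021 WHO-CNS classification will be the primary outcome"; grade is the secondary outcome.
- **Reference standard.** Study design provides for preoperative blood, and says that "postoperative tumor tissue samples will be collected to detect CTC characteristics and the latest glioma diagnosis based on the 2021 WHO-CNS tumor classification". No other route to the 2021 diagnosis is given.
- **Labels.** Model development preprocess states: "Each patient in the dataset had MR scans of four sequences: T1C, T1, T2, T2 flair, and tumor mask, along with classification labels". It continues: "According to the 2021 WHO classification criteria, the molecular types of glioma were divided into 11 subcategories", with three grades. Then: "The grades, segmentations, and subcategories labels of each patient were one-hot encoded".

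**The concern.** The study's case for itself is that a model is needed for the latest classification. Related study finds models built on the 2016 classification too limited for present needs. Against that background, the article admits cases from a database dated two years before the 2021 scheme and treats them as fully labelled under it.

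Two kinds of error could follow. Grades, or subcategories that combine several findings, could come from earlier criteria. Markers never tested could be coded as one of the known states. Either error would follow dataset lines. A network can learn to recognise the source of an image, so errors tied to source are harder to spot than errors spread at random. At stake is the first objective: whether the model is trained throughout on the diagnosis it is meant to predict.

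**Working it through.** The plan states no figure on this point, so the check sets the sections side by side.

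**1. Are BraTS cases in the classification task?** Participant criterion enrols them, the abstract uses them to develop the multi-task model, and the preprocessing section gives each patient grade and subcategory labels. Nothing excludes them.

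**2. Could the stated reference standard have produced their labels?** Study design obtains the 2021 diagnosis from postoperative tissue collected in the study. That cases in an existing public database supply no study tissue is an inference, but hardly avoidable. Their labels must come from somewhere the article does not mention.

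**3. Could those labels be 2021 labels?** This depends on the type of label.

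| Label | Effect of a 2019 origin |
|---|---|
| Grade (II/III/IV) | Not assigned under 2021 criteria unless relabelled later |
| Subcategory combining several findings | Same |
| Single marker state, such as IDH mutant or wild type | Unchanged by the scheme if tested; missing if not tested |

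Primary outcomes lists seven marker items and the preprocessing section 11 molecular subcategories. The article does not explain how the two lists map onto each other, so how many of the 11 are composite cannot be settled.

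**4. Does the model allow for an unknown label?** Not as printed. The coordinate and confidence losses carry indicator terms that select which boxes count. The classification loss sums over all types and classes with no indicator for whether a label is known. The one-hot encoding names no unknown category.

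**5. Does staged training keep BraTS labels out?** The learning-curve section trains backbone, detection and segmentation first and the classification part second, without saying which dataset feeds which stage. Even a first-stage-only role would not be clearly safe. Under Classification part, the detection network itself yields 14 class features (3 grade + 11 molecular = 14), and the total loss includes the classification term.

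**6. Size.** The share of affected training labels would be q × r, where q is the BraTS share of classification-training cases and r is the proportion of their labels that are wrong or unsupported. The article gives neither, and the sample-size statement of 400 is not broken down by source.

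The enrolment, tissue and each-patient statements therefore cannot all hold for BraTS as written.

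**The case against.** The strongest reply is that the article nowhere describes what labels BraTS holds. A 2019 date and the absence of study tissue do not show that tissue-based molecular results are lacking, and the preprocessing section says that the 2021 criteria were applied. Relabelling may have been done. This stands: a reader might infer that the model *is* trained on superseded labels, and the documents do not establish that. They support only that it may be.

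Other stronger readings also fail:

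- **All molecular labels mix two schemes.** A tested marker state does not change when a classification is revised. The scheme problem is confined to grade and composite subcategories; for single markers the problem is missing results.
- **Performance is measured against the wrong reference.** No section says that BraTS cases are scored for grade or molecular type. The abstract mentions them only for development.
- **Retrospective hospital patients have the same defect.** Data collection lists grade and the marker panel for glioma patients, which largely answers this.
- **A percentage of wrong labels can be given.** Assuming q of 20–50% and r of 10–25% gives 0.20 × 0.10 = 2% to 0.50 × 0.25 = 12.5%, but neither range has an anchor in the article.

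It can also be said that a condensed article may leave the dataset used at each training stage to a fuller document. That is fair for the staging alone. It does not dispose of the point, because the article makes positive statements (one tissue-based route, labels for every patient) that do not fit cases it also enrols.

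**Conclusion.** The concern holds as an unreconciled conflict with a real route to label error. BraTS 2019 cases enter development of a model with 2021 targets and are said to be labelled like everyone else, while the only stated reference standard cannot plausibly reach them. The first objective may therefore be trained partly on grades or composite subcategories from earlier criteria, or on untested markers encoded as known.

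The conclusion rests on two inferences: that public-database cases supply no tissue to this study, and that labels issued with a 2019 dataset are not 2021 labels without later relabelling. It assumes nothing about which labels BraTS contains. The size of the effect cannot be computed from the article.

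**What to change.** - State the role of BraTS: use it for the coordinate, confidence and segmentation losses.
- Mask its grade and molecular terms wherever they enter the loss, including the detection network's class outputs, not only in the final classification stage.
- Leave it out of grade and molecular accuracy, precision and recall.
- Allow an exception label by label: a BraTS case may count for a given label where the tissue-based results needed under the 2021 criteria are available and the label is assigned from them. Name the source of those results.
- Correct the preprocessing statements that give every patient classification labels, so that they say which labels each source carries.

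The work is a label mask and a written labelling rule. The price is fewer cases for classification training; segmentation and detection keep every case. If BraTS cases were meant to count towards the 400, which the article does not say, the number supporting the molecular outcome would fall by however many are masked, and that should be stated too.
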